# Scapular stabilization exercise based on the type of scapular dyskinesis versus traditional rehabilitation training in the treatment of periarthritis of the shoulder: study protocol for a randomized controlled trial

**DOI:** 10.1186/s13063-021-05654-2

**Published:** 2021-10-18

**Keywords:** Scapular stabilization exercise, Scapular dyskinesis, Periarthritis of the shoulder, Muscle imbalance

## Abstract

**Background:**

Periarthritis of the shoulder is a common disease leading to dysfunction of the shoulder joint and have a significant impact on patients’ daily life. Evidence shows that there is a close relationship between scapular dyskinesis (SD) and shoulder diseases. Scapular stabilization exercise has been proved to be efficacious in relieving pain and improving function. However, there is no targeted exercise based on the type of scapular dyskinesis. This study will investigate the potential of scapular stabilization exercise based on the type of scapular dyskinesis in treating periarthritis of the shoulder.

**Methods:**

This study is a prospective, randomized controlled, parallel-group trial, intending to recruit 90 patients diagnosed with periarthritis of the shoulder. Patients will receive scapular stabilization exercise training based on the type of scapular dyskinesis or receive traditional rehabilitation training conducted for 30 min, once a day, for 6 weeks. The primary outcome is Constant-Murley score (CMS), and other outcomes include pain degree, range of motion (ROM), type of scapular dyskinesis, scapula position, and patients’ satisfaction with shoulder function. Assessments will be performed at baseline, 2-, 4- and 6-week treatment, and at the 6-week follow-up after the end of treatment.

**Discussion:**

This study will be the first study to investigate the clinical efficacy of scapular stabilization exercise based on the type of scapular dyskinesis in patients with periarthritis of the shoulder. The results may provide evidence of the effect of targeted scapular stabilization exercise in improving shoulder function and correcting scapular dyskinesis, and provide valuable information for future research.

**Trial registration:**

This study had been registered in the Chinese Clinical Trials Registry. Registration number: ChiCTR2100044332 at March 14, 2021.

## Background

Generalized periarthritis of the shoulder is a sterile specific inflammatory reaction caused by long-term chronic injury or degeneration of the joint capsule around the shoulder joint and surrounding tendons, muscles, ligaments and other soft tissues [1]. It includes rotator cuff injuries, biceps tendonitis, supraspinatus tendonitis, shoulder impingement syndrome, shoulder instability, calcified tendonitis, acromioclavicular arthritis, and sternoclavicular arthritis. The annual incidence of PA is between 3 and 5% in the general population and it usually develops between the ages of 40 to 70 years. It is more common in women than men [2]. Patients often suffer from recurrent pain and limited shoulder movement, which affects daily life and work and brings economic burdens on individuals and societies [3]. Current conventional therapies include non-steroidal medications, physical agent therapy, and joint cavity injections, while the efficacy remains unsatisfactory [4]. In addition, joint cavity injections may lead to adverse events such as infectious arthritis [5].

On the other hand, the scapula plays an important role in maintaining complex shoulder kinematics [6]. Altered scapular motion and position have been termed scapular dyskinesis (SD) [7]. Kibler et al. [8] classified SD into 4 types. Type-1 represents the dorsal prominence of the inferior angle of the scapula. Type-2 represents the dorsal prominence of the entire medial border. Type-3 represents the elevated superior border of the scapula, and the scapula could also be anteriorly displaced from the posterior thorax. Type-4 represents the symmetry of bilateral scapula. According to data reported in the literature, SD may be important risk factors for periarthritis of the shoulder [9–11]. The scapular muscle group, consisting of the trapezius, serratus anterior (SA), pectoralis minor (PM), levator scapulae (LS), rhomboid muscle (RM), and teres major (TM), is mainly responsible for scapular movement and dynamic stabilization of the scapula. An optimal interaction between these muscles is needed to provide stability and mobility of the scapula both at rest and during shoulder movements [11]. Previous studies have reported excessive activation of upper trapezius (UT), PM, LS, TM, and decreased activity of middle/lower trapezius (MT/LT), SA, RM in subjects with SD, and different types of SD have different manifestations of muscle imbalance [12–17]. These altered muscle activation patterns are associated with altered scapular kinematics, including reduced scapular upward rotation, external rotation and posterior tilt [12]. Overall, SD is closely related to muscle imbalance and is usually associated with shoulder pathology [18]. However, it is unclear if SD is the cause or the result of shoulder pathology.

Turgut et al. (2017) [21]	30 subacromial impingement syndrome patients	Wall slides with squat, wall push-ups plus ipsilateral leg extension, lawnmower with diagonal squat, resisted scapular retraction with contralateral 1-leg squat, and robbery with squat.	Three-dimensional kinematics, the Turkish version of the Shoulder Pain and Disability Index (SPADI).	Scapular stabilization exercise therapy is an effective tool for controlling pain and improving disability status.
Hotta et al. (2018) [22]	50 patients with shoulder impingement	The neuromuscular exercises were towel slide, PNF scapular, inferior glide, and scapular clock. The strengthening exercises were diagonal D1, push-up plus, full can, prone horizontal abduction with external rotation from 90° to 135°, side-lying external rotation with abduction at 0°, diagonal D2 eccentric, scapular punch, and horizontal rowing.	Resting position and scapular kinematics, muscular strength, numeric pain rating scale, Shoulder Pain and Disability Index (SPADI).	Motor control and muscular strengthening training improve function among subjects with shoulder impingement syndrome.

In the present study design, we developed a randomized controlled trial to evaluate the effect of scapular stabilization exercise based on the type of SD in patients with periarthritis of the shoulder. We hypothesized that scapular stabilization exercise based on the type of SD would improve shoulder function and correct SD better than traditional rehabilitation training.

## Methods

### Study design

This is a prospective, multicenter, randomized controlled, parallel-group superiority trial, designed following the SPIRIT 2013 statement. The CONSORT flow chart is presented in Fig. 1. Figure 2 shows the schedule of enrolment, intervention, assessments, and study visits for the study groups. This study will be performed at Shanghai Jiao Tong University Affiliated Sixth People’s Hospital, the Lingang Branch of Shanghai Sixth People’s Hospital, Shanghai 8th People’s Hospital, Shanghai Xuhui District Dahua Hospital, and Shanghai Fengxian District Central Hospital from March 2021 to January 2023. Study participation will be promoted through advertisements. Participants will undergo screenings to confirm that they meet the inclusion criteria and exclusion criteria and will be provided written informed consent to participate. The purpose and content of the study of the study will be clarified by the first researcher to the subjects, and written informed consent will be obtained from them at the time of enrolment. In the consent form, the participants will be asked if they agree to use their data in case they withdraw from the study. Moreover, the research team will get their permission to share relevant data with other academic experts. This experiment does not involve collecting biological specimens. The study was approved by Ethics Committee of Shanghai Sixth People’s Hospital (2021-031) and registered in the Chinese Clinical Trials Registry (ChiCTR2100044332). Evaluators and data collectors will be blinded as to the groups and treatment allocation.

**Fig. 1 Fig1:**
[figure not shown]
Study flowchart

**Fig. 2 Fig2:**
[figure not shown]
Schedule of enrollment, intervention, study visits, and assessments for both study groups

Treatment groups will receive different treatment programs as follows:
Group 1: Scapular stabilization exercise based on the type of SD for once a day, for up to 6 weeks.Group 2: Traditional rehabilitation training for once a day, for up to 6 weeks.

### Inclusion criteria

Males and females aged 20 to 60 years old.Unilateral shoulder pain, with or without limited shoulder movement.Patients who meet the diagnostic criteria with broadly defined periarthritis of the shoulder, including rotator cuff injuries, biceps tendonitis, supraspinatus tendonitis, shoulder impingement syndrome, and shoulder instability.A maximum pain score of equal or less than 5/10 on a numerical rating scale (NRS)Patients volunteered to participate in the study and signed informed consent.

### Exclusion criteria

Rotator cuff tendon torn in all layers, fracture, dislocation, nerve injury, and other diseases that cause shoulder pain.History of trauma or shoulder surgery.Patients with scoliosis or acute cervical spondylosis.The flexion or abduction angle of the shoulder less than 90°.Patients that body surface markers are not obvious, which will affect the assessment, such as obesity (body mass index greater than 28).Other diseases that unfit or unable to complete the treatment plan, such as active infections, active inflammatory diseases, tumors, neurological disorders and changes in cognitive function (such as stroke, epilepsy, Parkinson’s disease, and peripheral neuropathy), systemic diseases involving joints (such as rheumatoid arthritis), and severe osteoporosis.Patients who refuse to accept the treatment.

### Exit criteria

Patients who are unable to adhere to the study protocol and study requirements;Patients who have severe adverse reactions after intervention and cannot successfully complete the treatment;Any new illness that affects their inclusion;The patient is lost to follow-up;

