### Interventions

Patients recruited to the trail will undergo a 3-day washout period before entering the treatment. If the patient is unable to adhere to the study protocol and study requirements during the washout period, the patient will withdraw from the study. All patients will be treated by the same therapist, who is not blinded to the treatment groups as the therapist will adjust exercise intensity. Patients will exercise at home once a day for 6 weeks and cone for further consultation every 2 weeks. In addition, physical therapy and anti-inflammatory drugs can be appropriately used according to the condition of the patient. To maintain the adherence of the patients to the intervention, the researcher team will regularly contact patients during the intervention via telephone or the WeChat between visits and online clocking software is used to ensure patient compliance.

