### Sample size calculation

The study is designed to achieve 95% power overall at the 0.05 significance level to detect change on the CMS between groups after 6 weeks. According to G*Power 3.1 software, we use repeated measurement analysis of variance (ANOVA) (Effect size = 0.25, Number of measurements = 4) to calculate the sample size. Considering a dropout rate of 20%, a sample size of 90 (45 per group) will be needed in this trial.

The statistical hypotheses are:
H0: mean CMS scale (scapular stabilization exercise) = mean CMS scale (traditional rehabilitation training).HA: mean CMS scale (scapular stabilization exercise) ≠ mean CMS scale (traditional rehabilitation training).

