### Safety monitoring

Patients will be informed of the potential risks and benefits of the trial and sign an informed consent form before participating in the research to protect their rights and interests.

Intervention involved in the study protocol is exercise therapy, so serious adverse events are rare. When potential adverse events occur in a patient, the researchers will record the severity, duration, treatment measures, and event outcomes. The doctor will determine the causal relationship between the treatment and the adverse event and decide whether the patient is suitable for continued participation in the study. Also, relevant information will be reported to the ethics committee.

The following are the criteria for terminating a patient from the study: (1) a serious adverse event happened that the researchers believes that the patient is not suitable for continued participation or the patient has requested to be withdrawn from the study; (2) the patient is found to have serious diseases during the study; (3) the patient has received other treatments that may affect the outcomes.

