### Statistical analysis

In this trial, we will implement the intention-to-treat analysis and statistical analysis will be carried out by a researcher not involved in the evaluation and treatment. Data will be recorded in the CRFs. Data analysis will be done using the SPSS version 26.0 statistical software. In order to incorporate the data of the participants into data analysis regardless of the protocol adherence, all the analyses will be performed in accordance with the intention-to-treat principle. Data will be expressed as frequencies and percentages for categorical variables, mean, and (±) standard deviation for continuous variables. Intergroup comparison of the type of SD will be calculated using chi-squared test. Intergroup comparison of pain, ROM, scapula position (LSST, SI, PMI), and patients’ satisfaction with shoulder function will be calculated using repeated measurement ANOVA. Intergroup comparison of time points will be calculated using Least Significant Difference. Statistical significance is defined as a *P* value of < 0.05.

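### Patients leave the study for inability to adhere or for other treatments, with no later assessment stated, so the intention-to-treat aim cannot be fully met

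*Protocol article*

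**What the plan says.** All references are to the protocol article.

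- **Exit criteria.** One of four grounds is "Patients who are unable to adhere to the study protocol and study requirements". The others are a severe adverse reaction that prevents completion, a new illness affecting inclusion, and loss to follow-up.
- **Interventions.** The same adherence wording is used for the 3-day washout, with its consequence spelled out. If the patient is "unable to adhere to the study protocol and study requirements during the washout period, the patient will withdraw from the study".
- **Safety monitoring.** A further list opens "The following are the criteria for terminating a patient from the study". Its third item is that "the patient has received other treatments that may affect the outcomes".
- **Interventions, on co-treatment.** During the programme, "physical therapy and anti-inflammatory drugs can be appropriately used according to the condition of the patient".
- **Statistical analysis.** All analyses are to follow intention to treat. The stated purpose begins "In order to incorporate the data of the participants into data analysis regardless of the protocol adherence".
- **Sample size calculation.** The trial is powered "to detect change on the CMS between groups after 6 weeks", with a 20% allowance for dropout and 90 patients in total.
- **Study design.** On consent, "the participants will be asked if they agree to use their data in case they withdraw from the study".

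The Outcome assessments section schedules visits at baseline, at weeks 2, 4 and 6, and 6 weeks after treatment ends. It does not say whether these visits go on for a patient who has exited.

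**The concern.** An intention-to-treat comparison needs outcomes from patients who stop exercising or turn to another treatment, because those events happen after randomisation and can be consequences of the allocated programme. Here the same events are grounds for leaving the study. If exit ends assessment, the outcomes that the analysis promises to include are never measured, and no statistical method can recover their values.

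The loss need not be balanced. One arm performs type-specific stretching and strengthening that progresses to resistance. The other performs pendulum, wall-climbing and stick exercises. Patients and therapist know the allocation. Exits for poor adherence or added treatment may therefore differ between arms in number, in the kind of patient, or in both. At stake is bias in the week-6 and follow-up comparisons of CMS.

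**Working it through.** **1. Does exit mean leaving the study?**

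- Safety monitoring is explicit: its list is about ending participation in the study, and receipt of other treatments is on it. This applies after randomisation.
- Exit criteria is less explicit. However, inability to adhere stands in the same list as loss to follow-up, which cannot mean merely stopping the exercises. Interventions attaches withdrawal from the study to the same adherence wording. Leaving the study is the natural reading, though it remains an inference.
- The washout sentence is used here only to show what the wording means. The article does not say whether randomisation precedes the washout, so washout withdrawals themselves may not touch the randomised comparison.

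**2. Do the other provisions fill the gap?**

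- The consent clause allows use of data already collected. A patient who exits at week 3 then contributes baseline and week 2, but no week-6 or follow-up CMS.
- The dropout allowance concerns numbers only. The plan's total can be reproduced with the repeated-measures noncentral F for the group-by-time interaction. Stated inputs are effect size f = 0.25, m = 4 measurements, two groups, alpha 0.05 and power 0.95. The correlation ρ between measurements is not stated, and ρ = 0 is assumed.
  - Noncentrality λ = f² × N × m / (1 − ρ) = 0.0625 × 72 × 4 / 1 = 18, with (m − 1) = 3 and (N − 2)(m − 1) = 70 × 3 = 210 degrees of freedom. Power is 0.956.
  - Inflation for dropout: 72 / (1 − 0.20) = 90, the stated total. (With ρ = 0.5 the same test would need 36, or 45 after inflation, so the match depends on the assumed ρ.)
  - The allowance is thus 0.20 × 90 = 18 patients. It protects power and does nothing about who is missing.

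**3. How large could the shift be?** The article gives no removal rates and no outcomes for removed patients, so this is illustration only.

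Let p be the proportion removed in an arm and D the completer mean minus the removed-patient mean on CMS. The mean of all patients in the arm is (1 − p) × completer mean + p × removed mean. Hence completer mean = arm mean + p × D, and

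bias in the group difference = p₁D₁ − p₂D₂.

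*Same D in both arms, removal rates differing.* Bias = (p₁ − p₂) × D. Assumed: a difference of 10 or 20 percentage points, which is 0.10 × 45 = 4.5 or 0.20 × 45 = 9 patients; D of 5 or 17 points.

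| Difference in removal | D | Shift (CMS points) | Share of the 17-point MCID |
|---|---|---|---|
| 0.10 | 5 | 0.5 | 2.9% |
| 0.10 | 17 | 1.7 | 10% |
| 0.20 | 5 | 1.0 | 5.9% |
| 0.20 | 17 | 3.4 | 20% |

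*Same removal rate, D differing between arms.* Bias = p × (D₁ − D₂). Assumed: 10% or 20% removed in each arm, with D differing by 5 or 10 points.

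- Lowest: 0.10 × 5 = 0.5 points, 0.5 / 17 = 2.9%
- Highest: 0.20 × 10 = 2.0 points, 2.0 / 17 = 11.8%

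Equal exit counts therefore do not guarantee an unbiased comparison. The minimal clinically important difference (MCID) of 17 points is the one given under Primary outcome measures.

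**The case against.** The strongest reply is that the argument leans on silence. This is a condensed article, and the full protocol may provide for assessment after exit. No sentence says that assessments stop, that data are discarded, or that exited patients leave the analysis set. The exit criteria set no adherence threshold and could be read as a catalogue of dropout reasons. Ordinary lapses are met with telephone or WeChat contact and clocking software, not removal. Earlier visits, the consent clause and the intention-to-treat commitment all preserve something, and any trial with missing outcomes falls short of a full intention-to-treat analysis. Every input to the illustration is assumed, it models completers only, and its extreme case is a fifth of the MCID.

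Part of this stands. The full protocol may resolve the matter, the reading of the exit criteria is an inference, and the size and direction of any bias are unknown. Values from weeks 2 and 4 could also reduce the shift if the analysis uses them.

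What does not stand is the claim of mere silence. Termination from the study for other treatments is written down, and so is an analysis meant to ignore adherence. Those two statements conflict unless assessment continues after exit. Missing outcomes occur in every trial, but here the plan's own rules create some of them, on grounds related to adherence and prognosis.

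The line between permitted physical therapy and anti-inflammatory drugs and the other treatments that end participation is unclear. That is an ambiguity, not a contradiction, and a list of permitted treatments is detail that an article may leave out. The conclusion does not depend on it.

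**Conclusion.** The concern holds. Followed as written, the exit and termination rules stop outcome collection for inability to adhere and for other treatment, so the intention-to-treat aim cannot be fully met for patients who exit before week 6 or before the follow-up visit. This rests on reading exit as leaving the study, which Safety monitoring states and Exit criteria implies, and on no contrary provision in the unseen full protocol.

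The size cannot be derived from the article. Under the assumed inputs the completer comparison moves by 0.5 to 3.4 CMS points when removal differs between arms, and by 0.5 to 2.0 points when removal is equal but the patients removed differ. These shifts are modest against a 17-point MCID. The point should be fixed because the remedy is cheap and outcomes not collected may never be recovered; it does not by itself invalidate the design.

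**What to change.** Amend Exit criteria and Safety monitoring so that inability to adhere and receipt of other treatments are reasons to stop the exercise programme only, and delete them as reasons to end data collection. State that every randomised patient who has not withdrawn consent is assessed for CMS and the other scheduled outcomes at weeks 2, 4 and 6 and at the visit 6 weeks after treatment ends. The same amendment could usefully say which co-treatments are allowed and which are not, with both recorded by arm, but this is secondary.

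The cost is a protocol amendment in a trial that Trial status describes as underway, plus attendance at already scheduled visits by patients who have stopped the programme. No new procedure is needed and the total stays at 90. Outcomes of patients who have already exited may not be recoverable, which is a reason to amend soon.

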### Interventions

Patients recruited to the trail will undergo a 3-day washout period before entering the treatment. If the patient is unable to adhere to the study protocol and study requirements during the washout period, the patient will withdraw from the study. All patients will be treated by the same therapist, who is not blinded to the treatment groups as the therapist will adjust exercise intensity. Patients will exercise at home once a day for 6 weeks and cone for further consultation every 2 weeks. In addition, physical therapy and anti-inflammatory drugs can be appropriately used according to the condition of the patient. To maintain the adherence of the patients to the intervention, the researcher team will regularly contact patients during the intervention via telephone or the WeChat between visits and online clocking software is used to ensure patient compliance.

